#### Secondary outcomes

Secondary outcomes are self-efficacy to be vaccinated for HPV and intention to be vaccinated after the intervention. The intention measure has two items that are typically used in HPV vaccine research and are based on the theory of planned behavior [28]. The questions query participants’ intention to initiate vaccination within 3 months and to complete the HPV vaccine series. The self-efficacy measure (3 items) [20, 36] was adapted from previous HPV studies among college students and young adults.

#### Mediators

We include 5 mediating variables: (1) *Knowledge* (8 items, one of which was tailored based on sex) will be assessed with true/false responses, and the percentage of correct responses will be calculated; (2) *HPV Vaccine Attitude* (3 items) measures attitudes towards the HPV vaccine; (3) *Perceived Social Norms* (Injunctive Norms − 3 items; Descriptive Norms − 2 items, tailored based on sex) measures participants’ perceptions of whether others in their social network would approve of the HPV vaccine and are based on scales with high item reliability among college students [37]; (4) *Safety Concerns* related to the HPV vaccine (5 items) [10, 38, 39]; and (5) *Perceived Susceptibility and Severity of HPV Infection* (6 items) [10] are adapted from previous HPV studies among college students and young adults.

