We planned an RCT to test the impact of a multilevel intervention for college students in Texas, where HPV vaccination rates are low [24, 25], and to identify how and for whom the intervention is effective. The intervention will test two major components: (1) narrative persuasion (individual level) and (2) enhanced access to the HPV vaccine (systemic level). A prior study found that female college students in the US who viewed video narratives from the perspective of peers and experts were twice as likely to obtain HPV vaccination compared to the control groups [20]. Building on this work, we conducted a pilot study using tailored written narratives from the perspective of peers and experts. The results suggested that the tailored written narratives have the potential to increase HPV vaccination intentions among young adults as well [26]. Qualitative data from our pilot study also suggested the need to overcome HPV vaccination access barriers at a system level [26]. These barriers include lack of access to the HPV vaccine on college campuses, difficulty navigating insurance, lack of insurance, lack of time to figure out where to get vaccinated, and lack of transportation [26]. These findings suggest that individual-level narrative interventions are potentially effective but that a system-level intervention to enhance access to HPV vaccines is needed to address barriers at the system-level [26]. Accordingly, the overall aim of this study is to assess the impact on HPV vaccination initiation and completion of a multilevel intervention that combines narrative persuasion and enhanced access to HPV vaccination. To our knowledge, this study is the first large-scale multilevel intervention to test the combination of narrative persuasion and enhanced access to address individual and system-level barriers to receiving HPV vaccination among college students.

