### Aims

The primary aim of this RCT is to evaluate the impact of addressing individual and system levels of influence on HPV vaccination initiation and completion rates **(Aim 1)**. First, we hypothesize that narratives (video or written) combined with access to the HPV vaccine will both improve HPV vaccination rates over standard CDC HPV information alone (control) (*Hypothesis 1.1).* Second, we hypothesize that narratives (video or written) will improve HPV vaccination rates compared to receiving the control, which is the CDC HPV information *(Hypothesis 1.2).* Third, we hypothesize that enhanced access to the HPV vaccines will increase HPV vaccination rates over vaccination rates achieved with usual care (no enhanced access) *(Hypothesis 1.3)*. The secondary aim of this RCT is to understand the underlying mechanisms of the intervention and explore characteristics of individuals who benefit from the intervention **(Aim 2)**. Guided by the behavioral theories (Theory of Planned Behavior [28], Social Cognitive Theory [29, 30], and Health Belief Model [31]), We hypothesize that theorized factors (i.e., HPV vaccination knowledge, attitudes, perceived social norms, safety concerns, and perceived susceptibility) will mediate group differences in HPV vaccination outcomes (Hypothesis 2.1). In addition, we have two research questions: *RQ1.* For whom is the intervention most effective and why? *RQ2.* What critical factors facilitate or hinder implementation of the intervention based on stakeholders’ perspectives?

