#### Enhanced Access to HPV Vaccine conditions

Enhanced access will be in the form of patient navigation, on-campus vaccine clinics, and financial assistance. At the end of the narrative intervention/CDC information sessions, participants in enhanced access condition will receive information about vaccination options automated through REDCap based on their self-reported insurance plan. Students with private insurance or Medicaid will be informed of dates for on-campus HPV vaccine clinics organized by the study staff in partnership with a local pharmacy and be offered the opportunity to pre-register to attend. Students who are uninsured will be assisted to apply for the Merck Vaccine Patient Assistance Program and will be navigated to the school health center to receive HPV vaccination. Participants will receive email reminders before the initial clinics. After participants complete the initial dose of the HPV vaccine, they will receive reminders to register for the second and third doses. Participants who are unable to attend the on-campus clinics for any reason or whose second or third dose are due during a school holiday will be contacted by study staff and given the option to get vaccinated at a participating pharmacy near them or be rescheduled for the next on-campus clinic. Participants will not have any out-of-pocket costs for receiving HPV vaccination.

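### The H2.1 mediation analysis has no mediator matched to what enhanced access changes, so a null indirect effect for access could come from the choice of measures

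*Protocol article*

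**What the plan says.** The Aims section states: "The secondary aim of this RCT is to understand the underlying mechanisms of the intervention". Under that aim, Hypothesis 2.1 holds that "HPV vaccination knowledge, attitudes, perceived social norms, safety concerns, and perceived susceptibility" "will mediate group differences in HPV vaccination outcomes (Hypothesis 2.1"). The hypothesis is not limited to the narrative factor.

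The Mediators section fixes the list: "We include 5 mediating variables". They are the constructs of the hypothesis, with perceived severity joined to susceptibility.

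The system-level factor is of a different kind: "Enhanced access will be in the form of patient navigation, on-campus vaccine clinics, and financial assistance". The Introduction names the barriers found in the pilot's qualitative data. Besides the lack of vaccine on campus, they include "difficulty navigating insurance, lack of insurance, lack of time to figure out where to get vaccinated, and lack of transportation".

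Self-efficacy has another role: "Secondary outcomes are self-efficacy to be vaccinated for HPV and intention to be vaccinated after the intervention". Table 2 (the SPIRIT schedule) collects it at T0 (baseline), T1 (post-intervention), T2 (3 months) and T3 (6 months), with no footnote restricting who is asked.

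Under Data analysis, Aim 2, mediators at T1 and at 3 months are related to outcomes at 3, 6 and 9 months. All Aim 2 tests are two-sided at 0.05 and declared hypothesis-generating.

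**The concern.** A mediation model can credit an effect only to the mediators it contains. The narratives are meant to persuade, so the five listed constructs suit them. Enhanced access offers clinic dates, pre-registration, navigation, reminders and vaccination without out-of-pocket cost. The article describes no component of it aimed at knowledge, attitudes, safety concerns or perceived susceptibility. There is thus little reason to expect a strong path from access to any listed mediator, and no listed mediator corresponds to the barriers that access is meant to remove.

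What is at stake is interpretation. If the indirect effects for access are null, the natural reading is that the access effect is not mediated, or that H2.1 fails for it. The data could not separate that from the mechanism simply not having been measured. The Discussion expects the mediators to explain the intervention's impact and to guide further tailoring, and for one of the two factors that expectation would rest on unmatched measures.

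**Working it through.** **Targets of access set against the mediators**

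| Barrier or component of access | Listed mediator that measures it |
|---|---|
| Vaccine unavailable on campus; on-campus clinics | None (descriptive norms might shift indirectly) |
| Insurance status and navigating insurance; financial assistance | None |
| Time to find a provider; patient navigation | None |
| Transportation | None |

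**Self-efficacy: availability and timing**

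- Table 2 schedules it at T0 to T3 without a footnote. Safety concerns, a listed mediator, is asked at T2 only of those who have not initiated.
- Access information comes at the end of the narrative or CDC session (Enhanced Access section). Table 2 puts all six conditions in the Intervention column, before T1. That T1 follows the access information is implied but not stated.
- Clinic attendance, later-dose reminders and rescheduling come after T1, so a T1 score can reflect only the offer of access.
- T2 coincides with the 3-month initiation outcome, so T1 is the cleaner time for initiation. For 9-month completion, T2 comes first: eligible participants have had no dose, and the schedule in the Introduction puts the third dose 6 months after the first.

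**Size of the factor concerned, on the planning rates**

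Inputs (Sample size calculation), in the order control, written, video, access only, access + written, access + video: initiation 12, 20, 22, 20, 40, 42%; completion 4, 10, 11, 15, 30, 32%.

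To confirm that the plan's marginal rates are simple averages of these, I recomputed its power: normal approximation with pooled variance, two-sided alpha 0.005, stated group sizes. The lowest of the ten values is for written narratives on completion (9.5% v 20%, 320 per group), at 82.9%; the others run from 92.0% upward. This agrees with the stated range of 82% to 99%.

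Main effect of access = mean of the three access cells minus mean of the three non-access cells:

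- Initiation: (20 + 40 + 42)/3 − (12 + 20 + 22)/3 = 34 − 18 = 16 points
- Completion: (15 + 30 + 32)/3 − (4 + 10 + 11)/3 = 25.7 − 8.3 = 17.3 points

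Marginal effects of narratives:

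- Initiation: written 30 − 16 = 14; video 32 − 16 = 16
- Completion: written 20 − 9.5 = 10.5; video 21.5 − 9.5 = 12

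These margins include an assumed synergy. The access effect at each narrative level is:

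- Initiation: 20 − 12 = 8 (no narrative); 40 − 20 = 20 (written); 42 − 22 = 20 (video); mean 16
- Completion: 15 − 4 = 11; 30 − 10 = 20; 32 − 11 = 21; mean 17.3

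Narratives alone against control give 8 (written) and 10 (video) on initiation, and 6 and 7 on completion.

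On completion, then, access has the largest assumed effect by either measure. On initiation its main effect only ties with video, and access alone equals written alone and falls below video alone. The documents give no assumed effect of any arm on any mediator, so the indirect effects themselves cannot be quantified.

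**The case against.** A reader might infer that Aim 2 cannot explain the system-level effect at all. The article does not support that. Aim 2 also has RQ1 (for whom and why) and RQ2 (what helps or hinders implementation). The abstract says the interviews and focus groups are meant to clarify mechanisms, and the analysis also draws on work logs and meeting minutes. Since pilot interviews are what identified the access barriers, a qualitative route is reasonable. This part of the objection stands. It is still only a partial answer: interviewees are chosen by vaccination status, the student interviews are to be analysed by gender, sexual activity and ethnicity, access condition is mentioned in neither place, and interviews cannot estimate the indirect effects that H2.1 puts forward.

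A reader might also infer that the access paths will be null by design. That too goes beyond the text. Mediators are used again at 3 months, when clinics or contact with navigators and vaccinators could have shifted norms, attitudes or safety concerns, and a condensed article does not show what navigators say. A null is a reasonable expectation, not a certainty. Nor would it be empty, since it would fit the rationale that access works on structural barriers. But it would not identify those barriers as the pathway.

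Finally, self-efficacy may be a weak stand-in. Its three items are not shown, so whether they touch on cost, navigation or availability is unknown. This stands and limits what the fix can deliver.

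**Conclusion.** The point holds for the quantitative mediation analysis under H2.1, and only there. The hypothesis spans all group differences, the mediator list is closed at five, and none measures what enhanced access changes. A null indirect effect for the access or combination contrasts would be ambiguous between absence of mediation and absence of a relevant measure.

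The factor concerned is assumed to add 17.3 points to completion and 16 to initiation as a main effect, or 11 and 8 without narratives. These are planning assumptions, and the larger figures include synergy in arms for which the five mediators are relevant. The consequence is confined to a secondary, hypothesis-generating aim. The conclusion assumes that enhanced access works mainly through the practical barriers named in the Introduction.

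**What to change.** Check two facts first: what the three self-efficacy items ask, and whether T1 is completed after the access information is shown.

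If both are satisfactory, add self-efficacy as an exploratory mediator for the access and combination contrasts, in the single- and multiple-mediator models. Use T1 adjusted for T0 for 3-month initiation, and T2 adjusted for T0 for 9-month completion. Keep it as a secondary outcome, and state that it is only a partial proxy for access barriers. At T2 some participants will already have had a first dose, so an indirect effect through the T2 score may partly run through initiation; the report should say so.

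If either check fails, limit the H2.1 mediation claim to the narrative factor and state that access mechanisms are examined only qualitatively.

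The cost is a change of wording and one more exploratory mediator at the 0.05 level, on data already being collected. The T2 score will be missing for those lost by 3 months (15% assumed). The ten Aim 1 tests at 0.005 (10 × 0.005 = 0.05), the sample size and the power are unchanged. New barrier items are a weaker option, because recruitment began in March 2022 and they would miss earlier enrolees.

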#### Covariates

Potential covariates are demographic variables (age, sex, year in college, ethnicity, insurance coverage, household income, parents’ level of education) and sexual history (sexually active or not).

#### Data quality

To ensure data quality, we will include two attention check questions: one in the first half of the questionnaire and the other in the last half. An example of the attention check questions is “On this item, please answer “Strongly Disagree.” The questions will help verify if participants are reading the questions. Participants who answer one or both attention check questions incorrectly will be removed from the data analysis.

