### Sample size calculation

Our sample size calculations are mainly based on hypothesis testing for both vaccination initiation and vaccination completion in Aim 1, with a two-sided alpha of 0.005 (= 0.05/10) (with a Bonferroni adjustment) for each test. This adjustment is used because Aim 1 has 10 tests in total, including five comparisons specified in hypotheses for each of the two HPV vaccination outcomes. The five comparisons are for two simple effects (i.e., written/video narrative + access vs. control), two marginal effects (i.e., written/video narrative vs. no narrative), and a main effect (access vs. no access). The assumed HPV vaccination rates for these comparison groups are calculated based on the expected vaccination rates inferred from the literature [20, 21, 33, 34] for the six groups (i.e., control, written narratives, video narratives, access only, access + written, and access + video): 12%, 20%, 22%, 20%, 40%, and 42% at 3-month follow-up for initiation, and 4%, 10%, 11%, 15%, 30%, and 32% at 9-month follow-up for completion, respectively. Post-attrition sample sizes used for power analysis represent the worst-case scenario and thus provide conservative estimates. Assuming 15% and 20% attrition at 3- and 9-month follow-ups, a total sample size of 1200 at baseline yields 1020 for analysis of vaccination initiation (1200*85%=1020) and 960 for completion (1200*80%=960), respectively. Sample sizes available per group for each comparison/test (written/video narratives + access vs. control, written/video narrative vs. no narratives, access vs. no access) are 170, 340, and 510 for HPV vaccination initiation and 160, 320, and 480 for HPV vaccination completion, respectively. Power analysis using nQuery 7.0 [35] shows that these sample sizes will have excellent power (82%~99%) to detect group differences in each of the 10 tests.

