### Data collection

Participants who are eligible and agree to participate in the study will be asked to complete an informed consent form on REDCap. After signing the informed consent form, participants will complete online questionnaires on REDCap. Participants will first complete a brief demographic survey (i.e. sex, sexual activity status) in order to receive tailored narratives. Participants will then complete a baseline survey (T0), view the materials for their assigned group (described above), and complete the post-intervention survey (T1). At 3-, 6-, and 9-month, follow-up surveys will be administered. These will be sent as links to participants via email or text message (depending on the preference of the participants). At the 3-, 6- and 9-month follow-ups, all participants who report initiating or completing the HPV vaccine series will be asked to consent to releasing their medical records on HPV vaccination from the clinic, pharmacy, or doctor’s office where they were vaccinated.

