### Data analysis

Prior to the inferential procedures, extensive descriptive statistical analyses will be performed on all variables of interest. Distributional assumptions will be evaluated, and if indicated, normalizing (such as log) transformations or robust procedures will be employed (e.g., for the continuous mediating variables). Appropriate procedures to assess the validity and reliability of the questionnaires will be used. As a general strategy for our primary analysis, an intention-to-treat (ITT) approach will be used.

#### Aim 1

Logistic regression analysis will be used to test the five comparisons on both the HPV vaccination initiation and completion rates (binary: yes vs. no), controlling for the stratification factors (gender, sexual activity status, and race/ethnicity) and additional covariates as appropriate [40]. While we do not anticipate a strong cluster (university) effect, we will explore the above comparisons using generalized linear mixed models (GLMMs) with a binomial outcome distribution with a logit-link function to account for potential within-university correlations. Each of the hypotheses in Aim 1 will be tested at a 2-sided 0.005 significance level to ensure statistical reproducibility by controlling the overall type I error rate at 0.05.

#### Aim 2

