#### Handling of missing data and attrition

Participants in the study may be lost to follow-up, resulting in missing data. Consistent with the ITT approach to our primary analysis, we designate a participant’s group based on his/her randomization assignment despite potential group switch. We will impute missing data using an appropriate multiple imputation approach, assuming a missing-at-random mechanism [44]. Additional analyses will be conducted based on the observed data, which will give asymptotically unbiased estimates of the effects of interest, provided that missingness depends only on the observed variables included in the model. However, missing data may not be missing at random (e.g., participants who do not initiate or complete vaccination may choose to leave the study early); thus, we will conduct sensitivity analyses assuming different missing data mechanisms, especially when attrition is moderate or high (e.g., > 20%) and unbalanced across intervention conditions. We will explore pattern-mixture or selection models to account for potential missing-not-at-random (MNAR) mechanisms [44]. Similar results from the sensitivity analyses would strengthen our study findings.

To answer RQ1 and RQ2, we will conduct a content analysis of the qualitative data (interviews, meeting minutes, work logs, etc.) using a phenomenological method and a systematic approach to capture the themes. Interview data from students will be content analyzed in the context of gender, sexual activity status, and ethnic differences to inform future strategies to refine HPV vaccination intervention. Using inductive methods will shed light on successes and lessons learned in this study and help to clarify factors that facilitate or hinder implementation and dissemination of the intervention.

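### The rule that removes participants who fail an attention check has no exception for the primary outcomes, contradicts the intention-to-treat analysis, and is not counted in the sample size

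*Protocol article*

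**What the plan says.** All references are to the Protocol article.

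- **Data quality (under Measures):** "we will include two attention check questions: one in the first half of the questionnaire and the other in the last half". The consequence of failing is: "Participants who answer one or both attention check questions incorrectly will be removed from the data analysis". The rule removes persons, not questionnaires. It is not limited to the attitude or mediator scales, and it does not say at which survey wave the checks are asked.
- **Data analysis:** "As a general strategy for our primary analysis, an intention-to-treat (ITT) approach will be used".
- **Handling of missing data and attrition:** participants are analysed by randomised assignment, and "We will impute missing data using an appropriate multiple imputation approach, assuming a missing-at-random mechanism".
- **Sample size calculation:** the only deductions are 15% attrition at 3 months (1200 to 1020) and 20% at 9 months (1200 to 960). Of these numbers it says: "Post-attrition sample sizes used for power analysis represent the worst-case scenario and thus provide conservative estimates". Stated power is 82% to 99% over ten tests.
- **Table 2 (schedule):** the Randomization column stands before T0, the baseline survey. T1 follows the assigned materials, and T2 to T4 are the 3-, 6- and 9-month surveys.
- **HPV vaccination initiation and completion:** both primary outcomes are self-reported and verified by medical record review. The option to release or upload a record goes to students who report vaccination.

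**The concern.** Two analysts working from this article would analyse different populations for both primary outcomes. One, following the data-quality rule, drops every randomised participant who missed a check item. The other, following the ITT and missing-data sections, keeps them all. Read literally, the plan imputes an outcome for someone who disappeared, yet discards someone whose vaccination status was reported and perhaps confirmed from records.

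A missed check item is a reason to doubt attitude and knowledge scores. It does not make vaccination status unknown.

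Three things are at stake: the protection of randomisation in all ten confirmatory tests, the population to which the uptake rates apply, and the power statement, which takes no account of these removals.

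**Working it through.** **1. Timing of the removals.** Table 2 puts randomisation before T0. The Data collection section places a short demographic survey ahead of T0. Stratification needs sex and sexual activity status, so that short survey must precede assignment. Check items placed in the two halves of a questionnaire most naturally belong to T0 or a later survey, and all of those follow randomisation in Table 2.

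**2. Reproducing the stated power floor.** Alpha is given as "with a two-sided alpha of 0.005 (= 0.05/10) (with a Bonferroni adjustment) for each test". The assumed completion rates are 4% (control), 10% (written), 11% (video), 15% (access only), 30% (access + written) and 32% (access + video). The weakest of the ten tests is completion, written versus no narrative, with 320 per group:

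- written: (10% + 30%)/2 = 20.0%
- no narrative: (4% + 15%)/2 = 9.5%

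Power of the pooled-variance two-proportion z-test is Φ{[d√n − z·√(2p̄(1−p̄))] / √(p₁(1−p₁) + p₂(1−p₂))}, where:

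- d = 0.105, p̄ = 0.1475, z = 2.807
- √(2 × 0.1475 × 0.8525) = 0.5015
- √(0.095 × 0.905 + 0.20 × 0.80) = 0.4960

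At n = 320: (0.105 × 17.889 − 2.807 × 0.5015)/0.4960 = 0.949, so power is **82.9%**. This agrees with the stated 82%. Other methods give 83.7% (unpooled), 81.0% (Fisher exact) and 79.9% (continuity-corrected). The other nine tests run from 92.0% upwards.

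**3. Adding the removals.** The article gives no failure rate, so 5% to 20% is an assumption. Removals are taken as equal in both groups and on top of the stated attrition, with n = 320(1 − f). The answer depends on how often failers vaccinate. If they vaccinate at a fraction k of the overall rate, the analysed rate is p(1 − kf)/(1 − f).

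| Removed (f) | n per group | Failers at overall rate (k = 1) | Failers at half the rate (k = 0.5) | No failer vaccinated (k = 0) |
|---|---|---|---|---|
| 0% | 320 | 82.9% | 82.9% | 82.9% |
| 5% | 304 | 80.3% | 81.9% | 83.3% |
| 10% | 288 | 77.5% | 80.8% | 83.8% |
| 20% | 256 | 70.9% | 78.7% | 85.0% |

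With k = 1, power drops below the stated 82% once fewer than 315 per group remain (1 − 315/320 = 1.6% removed). It drops below 80% once fewer than 303 remain (1 − 303/320 = 5.3%). With k = 0, the analysed rates rise as n falls (at 10%: 0.095/0.90 = 10.6% and 0.20/0.90 = 22.2%) and power is not lost.

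**4. The other nine tests.** On the same pooled formula with k = 1 and 20% removed, the next weakest (completion, video versus none) has 83.1%. The one after that (initiation, written versus none) has 86.2%. None falls below 82%.

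**5. Bias if failure depends on arm (all inputs assumed).** Take a true rate of 20% in both arms, no failer vaccinated, and failure of 10% versus 5%. The analysed rates are 0.20/0.90 = 22.2% and 0.20/0.95 = 21.1%, a spurious gap of about 1.2 points. The planned contrast in the weakest test is 20.0 − 9.5 = 10.5 points.

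**The case against.** The strongest reply is that the conflict is one of wording and its harm is unproven.

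- **Bias.** No wave is named for the checks. If they are asked only at T0, they precede the materials, and the Randomization section says participants are not told their condition. Failure should then not depend on arm, and removal narrows the population without distorting the contrasts. This stands: a reader might infer that the primary comparisons are biased, but the article does not support more than a possibility that depends on placement.
- **Power.** A reader might also infer that the trial loses its stated power. The losses in the k = 1 column assume that failers vaccinate like everyone else. The usual worry about such exclusions is that failers vaccinate less, and in the extreme case there is no loss at all. In addition, a failer who would have been lost to follow-up anyway is already inside the 15% or 20%, so the deductions are an upper bound. Both points stand, and only one test of ten is exposed.
- **Outcome quality.** Nine-month completion is defined by self-report, and records are sought only from those who report vaccination, so an inattentive denial is never checked. Keeping failers can therefore add some misclassification. This also stands, but it argues for a sensitivity analysis, not for removal from the primary comparison.

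Leaving the matter to an analysis plan does not answer the point. The article states both rules outright, and they conflict.

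**Conclusion.** The contradiction holds. An unrestricted, post-randomisation exclusion stands beside an ITT commitment that covers both primary outcomes, and the sample size section does not count it, so its worst-case label is not justified while the rule stands. This rests on the text and on the order of columns in Table 2.

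The size of the harm is conditional. For the weakest test, power at 10% removal lies between 77.5% (failers vaccinate at the overall rate) and 83.8% (none vaccinate), against 82.9% as planned. The other nine tests keep more than 82% with up to 20% removed. Bias between arms is a risk only if the checks come after exposure to the assigned materials. Neither lost power nor biased contrasts should be reported as established.

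**What to change.** State that all randomised participants stay in the primary ITT analysis of initiation and completion whatever their attention-check result. Limit the exclusion to (a) a sensitivity analysis of the primary outcomes and (b) the survey-scale (Aim 2) analyses. Name the survey wave or waves that carry the checks, so that readers can judge whether failure could depend on arm.

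The stated 82% to 99% then needs no further deduction for these removals, and 1200 need not change. If the removal rule were kept for the primary outcomes, holding the planned analysed numbers would take 1200/(1 − f) randomised: 1264 at 5% and 1334 at 10%. The worst-case wording would also have to go.

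The cost is a sentence or two and no new data. Some self-reported outcomes from inattentive participants may be misclassified, which the sensitivity analysis addresses. The rule should be settled before outcomes are analysed; the article expects data management to finish by August 2026.
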